## Abstract

**Background:** Although revascularization treatment is recommended as the first-line therapy for patients with non-minor acute ischemic stroke (AIS), it only benefits a minority of patients. Previous studies have reported the positive effects of *Panax notoginseng saponins* (PNS) (Xueshuantong lyophilized powder) on AIS, however, there have been no rigorous trials. This study aims to assess the efficacy and safety of PNS therapy for patients with AIS.

**Methods:** The Evaluation of Xueshuantong in Patients with acutE ischemiC sTroke (EXPECT) trial is a multicenter, randomized, placebo-controlled, double-blind study aiming to enroll 480 patients in China. Eligible patients with AIS within 72 h of symptom onset will randomly receive either PNS or PNS placebo for 10 days and subsequently be followed up to 90 days. The primary outcome will be a change in the National Institute of Health Stroke Scale (NIHSS) score from baseline to 10 post-randomization days. The secondary outcomes include early neurological improvement (proportion of patients with NIHSS score 0–1), and Patient-Reported Outcomes Scale for Stroke score at 10 post-randomization days, the proportion of patients with life independence (modified Rankin Scale score of 0–1), the proportion of patients with a favorable outcome (Barthel Index ≥90), and Stroke-Specific Quality of Life score at 90 days. Adverse events or clinically significant changes in vital signs and laboratory parameters, regardless of the severity, will be recorded during the trial to assess the safety of PNS.

**Conclusions:** To our knowledge, this study is the first double-blind trial to assess the efficacy and safety of PNS in patients with AIS. Findings of the EXPECT trial will be valuable in improving evidence regarding the clinical application of PNS therapy in patients with AIS ineligible for revascularization treatment in the reperfusion era.

## Introduction

Stroke is the second leading mortality cause worldwide and ranks first in China (Zhou et al., 2019; GBD 2019 Diseases and Injuries Collaborators, 2020). The high rates of stroke prevalence, incidence, and disability cause a significant economic burden (Rajsic et al., 2019; Wu et al., 2019a). Ischemic stroke is the most common stroke subtype, accounting for approximately 70% of all stroke cases (Wang et al., 2017). Currently, revascularization treatment within 24 h of symptom onset is recommended for saving the penumbra to improve functional outcomes in patients with non-minor acute ischemic stroke (AIS) (Powers et al., 2019). Since 1995, intravenous thrombolysis has been administered as the first-line therapy for AIS (NINDS, 1995). However, it benefits a limited number of patients given the narrow time-window, prevalent patient delay, imaging dependence, and risk of hemorrhagic transformation (Yaghi et al., 2017; Powers et al., 2019). Additionally, despite the extended time-window of endovascular thrombectomy, it has limited clinical application since it requires superior surgical skills, advanced catheter, rapid neuroimaging evaluation of the core infarction territory, and extensive economic resources (Report on Stroke Prevention and Treatment in China Writing Group, 2020). Patients with non-minor stroke presenting a National Institute of Health Stroke Scale (NIHSS) score higher or equal to four are likely to have unfavorable functional outcomes once they miss the critical treatment opportunity at the acute stage. Therefore, there is a substantial need to develop effective and safe therapies benefiting a large number of patients with AIS.

The pathophysiology of cerebral ischemic injury is a complex and dynamic process, during which, the temporal and spatial evolution of a rapid cascade of events including energy failure, excitotoxicity, oxidative and nitrative stress, and inflammatory response is associated with tissue damage following cerebral ischemia (Dirnagl et al., 1999; Lo et al., 2005; Chamorro et al., 2016). Among them, inflammatory injuries are triggered within minutes and last for weeks. Injured brain cells extensively produce pro-inflammatory cytokines, including interleukin-6 (IL-6) and tumor necrosis factor-alpha (TNF-α), which results in neuronal damage. Consequently, there is an increased expression of adhesion molecules, including intercellular adhesion molecule 1 (ICAM-1), on the endothelial cell surface, which increases endothelial cell permeability, and therefore exacerbates ischemic injury (Barone et al., 1997; Dirnagl et al., 1999). Additionally, the accumulation of inflammatory mediators leads to blood-brain barrier disruption during the early phase after stroke onset (Brea et al., 2009; Giraud et al., 2015). As a result, leukocytes infiltrate the injured brain region and aggravate blood-brain barrier disruption in turn by releasing pro-inflammatory cytokines and matrix metalloproteinases (Neumann et al., 2015). Apart from focal inflammation, the so-called global inflammation responses occur and persist throughout the entire brain, affecting patients’ clinical outcomes (Shi et al., 2019). Therefore, neuroinflammation is deemed as the potential treatment target (Jayaraj et al., 2019).

*Panax notoginseng saponins* (PNS) (Xueshuantong lyophilized powder) isolated from the roots and rhizomes of Panax notoginseng (Burkill) F.H.Chen consists of five main components: notoginsenoside R1, ginsenoside Rg1, ginsenoside Rd, ginsenoside Rb1, and ginsenoside Re (*see* Additional File 1 in Supplementary Material). The systematic pharmacokinetics of PNS indicates that the main circulating constituents are unchanged saponins, and intravenous PNS administration guarantees drug stability without inducing cytochrome P450 3A (Pintusophon et al., 2019; Zhang et al., 2020). PNS has been shown to exert strong anti-inflammatory effects against atherosclerosis-related cardiac-cerebral vascular disease (Wan et al., 2009; Wang et al., 2011). Both *in vitro* and *in vivo* studies have proved that PNS and notoginsenoside R1 significantly reduced the levels of IL-6, TNF-α, and ICAM-1 via microRNA downregulation, inhibiting NF-κB signaling pathway activation, and increasing the anti-inflammatory factor levels (Huang et al., 2015; Shi et al., 2017; Fu et al., 2018; Meng et al., 2019). Besides, PNS and ginsenoside Rb1 have been reported to attenuate ischemia-reperfusion-induced degradation of endothelial tight junctions by inhibiting matrix metalloproteinase-9 (MMP-9) expression and increasing the tissue inhibitor levels of metalloproteinase, which alleviates blood-brain barrier disruption (Chen et al., 2015; Wu et al., 2019b). Other studies have demonstrated the neuroprotective effects of PNS concerning antioxidant capacity (Zhang et al., 2019), anti-apoptosis (Chen et al., 2011), and endothelial cell protection (Hu et al., 2018).

PNS administration to patients with AIS within 72 h of symptom onset improves local brain perfusion and promotes the structural plasticity of white matter fibers (Gui et al., 2013; Ren et al., 2018). However, these findings were reported by small-scale, open-label, single-center studies, which limited the robustness of the conclusions. It remains unclear whether patients with non-minor stroke could benefit from PNS therapy. Therefore, there is a need for a large-scale, well-designed, randomized controlled trial with clinical endpoints to determine the effects of PNS on patients with AIS. We further hypothesize that short-term treatment with PNS for patients with AIS could effectively decrease the NIHSS score. We, therefore, designed the **E**valuation of **X**ueshuantong in **P**atients with acut**E** ischemi**C** s**T**roke (EXPECT) trial to assess the efficacy and safety of PNS in patients with AIS.

## Methods and Design

### Study Design

The EXPECT trial (Clinicaltrials.gov, NCT04415164) is a prospective, multicenter, randomized, placebo-controlled, double-blind study to test the hypothesis that PNS is superior to placebo in decreasing the NIHSS score of patients with AIS after 10 days. This trial protocol was approved by the institutional review board of Dongzhimen Hospital, Beijing University of Chinese Medicine, Beijing, China (No. DZMEC-JG-2019-51-01). We described this protocol according to the SPIRIT 2013 Statement (Chan et al., 2013) and the complete checklist is available (*see* Additional File 2 in Supplementary Material).

### Patient Selection

We will recruit patients diagnosed as AIS with an NIHSS score of 4–16 (a total score of upper and lower limbs ≥2 on motor deficits), who can be randomized within 72 h of symptom onset, which is defined based on the “last seen normal” principle. The age of recruited patients will be limited to 18–80 years. All patients or their legally authorized representatives will provide written informed consent before any study-specific procedure. Table 1 lists the detailed inclusion and exclusion criteria.

**TABLE 1 T1:** Inclusion and exclusion criteria of the EXPECT trial.

**Inclusion criteria**
Acute ischemic stroke confirmed by head CT or MRI
Female or male patient aged ≥18 years and ≤80 years
Time from symptom onset to the randomization ≤72 h
4 ≤ NIHSS score ≤16 (total score of upper and lower limbs on motor deficits ≥2) at the randomization time
Signed informed consent
**Exclusion criteria**
Having already received thrombolysis or endovascular treatment before randomization
Secondary stroke caused by a tumor, traumatic brain injury, hematological disease, or other diseases with a confirmed diagnosis
Preceding mRS score ≥2
Other conditions that cause motor dysfunction (claudication, severe osteoarthrosis, rheumatoid arthritis, gouty arthritis, etc.).
Known severe liver or kidney dysfunction
Known allergies for ingredients in the investigational product, allergy history for food or medicine
Known medical condition likely to limit survival to less than 3 months
Known massive cerebral infarction combined with disturbance of consciousness (1a ≥2 in the NIHSS), dementia, mental impairment, or unsuitability for participation as judged by the investigators
Pregnancy or breastfeeding
Having participated in another clinical trial within 3 months before randomization

NIHSS, National Institute of Health Stroke Scale; mRS, modified Rankin Scale.

### Randomization, Allocation, and Blinding

The investigators will randomize 480 eligible patients and assign them to the intervention and control groups at a 1:1 ratio using block randomization with stratification according to medical centers. The randomization schedule will be generated by an independent statistician using SAS software version 9.4 (SAS Institute Inc.) and kept in sealed, sequentially numbered, opaque envelopes. Investigational medicine blinding will be completed at a pharmaceutical factory based on the randomization schedule and sent to medical centers along with the emergency envelopes. The block size will be closed to ensure concealment throughout the entire trial period. All investigators, participants, caregivers, and data analysts will be blinded to the treatment assignments throughout the trial until the blind codes are unconcealed. Investigators can request emergency unblinding in case of serious adverse events (SAEs) suspected to be associated with investigational medicine. Figure 1 presents a flowchart of the EXPECT trial.

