### Study Settings and Recruitment Strategies

Inpatients will be recruited from 11 tertiary hospitals throughout eight provinces in China. Additionally, poster advertisements will be placed in these medical centers to allow the patients to voluntarily contact investigators. Potential patients will be screened for eligibility based on the inclusion and exclusion criteria. Eligible patients will be informed regarding the risks and benefits of the study. Subsequently, patients or their legally authorized representatives will sign the informed consent form if they agree to participate in the study. Patient enrollment of the EXPECT trial began in September 2020. Until December 2020, 13 patients had been enrolled and the estimated primary completion will be October 2022. Figure 2 presents a schematic diagram of the patient timeline.

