### Statistical Analysis Plan

All randomized patients who receive at least one treatment dose and have safety outcome data will be included in the safety set. All patients in the safety set will be included in the full analysis set if efficacy outcome data are available. All patients in the full analysis set who are deemed to have no major protocol violations will be included in the per-protocol set. Efficacy and safety analyses will be performed according to the intention-to-treat principle. Additionally, per-protocol data analysis will be conducted as a reference. The last observation carried forward approach will be used to impute missing data of primary outcome. Regarding the primary outcome variable, between-group comparisons of the change in NIHSS score will be performed using Student’s *t*-test or Mann-Whitney *U* test, as appropriate. Regarding secondary outcome variables, between-group comparisons of the proportion of patients with an NIHSS score of 0–1, mRS grade ≤1, and BI score ≥90 will be performed using the chi-square test or Fisher exact test. Further between-group comparisons of the PRO-Stroke and SS-QOL score, as well as changes in biological indexes, will be compared using the *t*-test or Mann-Whitney *U* test. Moreover, between-group comparisons of the incidence of AEs will be compared using the chi-square or Fisher exact test. The effect of missing data on the results will be assessed through sensitivity analysis. All statistics will be 2-sided and statistical significance will be set at *p* < 0.05. Statistical analyses will be performed using SAS software version 9.4 (SAS Institute Inc.).

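### Randomization is stratified by centre but every named test ignores centre, so if centres differ in outcome the standard errors are on average somewhat too large

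*Protocol article*

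**What the plan says.** Under Randomization, Allocation, and Blinding, the protocol article assigns patients "at a 1:1 ratio using block randomization with stratification according to medical centers". Centre is the only stratification factor. Study Settings and Recruitment Strategies gives the number of strata: "Inpatients will be recruited from 11 tertiary hospitals throughout eight provinces in China".

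The section headed Statistical Analysis Plan names a test for each type of outcome:

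- Primary outcome: "between-group comparisons of the change in NIHSS score will be performed using Student’s" t-test or the Mann-Whitney U test.
- Binary secondary outcomes (NIHSS 0–1, mRS, Barthel Index): "mRS grade ≤1, and BI score ≥90 will be performed using the chi-square test or Fisher exact test".
- Continuous secondary and biological outcomes: "Further between-group comparisons of the PRO-Stroke and SS-QOL score, as well as changes in biological indexes" get the t-test or Mann-Whitney U test.
- Adverse events: "between-group comparisons of the incidence of AEs will be compared using the chi-square or Fisher exact test".

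None of these tests is stratified or carries a centre term, and the article mentions no centre-adjusted analysis.

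**The concern.** Blocking within centre gives each hospital nearly equal numbers in the two arms. A difference between hospitals in average recovery then adds almost equally to both arm means and cancels from the treatment difference. The two-sample tests treat the arms as independent samples and leave the between-hospital variation in the error term, so the analysis does not match the design.

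Differences between hospitals are plausible. The sites lie in eight provinces, patients may enter up to 72 hours after onset with NIHSS 4 to 16, and background care is delivered locally. What is at stake is precision: intervals wider than the design warrants, a test whose real size is below the nominal 5%, and some lost power.

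**Working it through.** **Inputs.** From Sample Size Calculations: mean decreases of 3 and 2.1, so a difference of 0.9; SD 2.5; two-sided α 0.05; power 90%; 480 patients; 20% dropout. Evaluable patients: 480 × 0.80 = 384, or 192 per arm. The between-centre share of outcome variance (ICC) is not in the article; 0 to 0.20 is assumed.

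**The plan's own figure.** The normal formula gives 163 per arm, 326 evaluable, and 326 / 0.80 ≈ 408 randomized. The stated 480 does not follow from its stated inputs. That is a separate matter, but it explains why power at 192 per arm is about 94% and not 90%.

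**Formulas for the primary t-test** (normal approximation, arms balanced within centre):

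- SE the t-test reports: S = 2.5 × √(2/192) = 0.2552
- True SE under blocking: S × √(1 − ICC)
- True size: 2 × [1 − Φ(1.96 / √(1 − ICC))]
- Power, planned test: Φ[(0.9/S − 1.96) / √(1 − ICC)]
- Power, centre-adjusted test: Φ[0.9 / (S√(1 − ICC)) − 1.96]

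With 0.9 / 0.2552 = 3.527:

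| Assumed ICC | Reported SE | True SE | Excess | True size | Power, planned | Power, adjusted |
|---|---|---|---|---|---|---|
| 0 | 0.255 | 0.255 | 0% | 5.0% | 94.1% | 94.1% |
| 0.02 | 0.255 | 0.253 | 1.0% | 4.8% | 94.3% | 94.6% |
| 0.05 | 0.255 | 0.249 | 2.6% | 4.4% | 94.6% | 95.1% |
| 0.10 | 0.255 | 0.242 | 5.4% | 3.9% | 95.1% | 96.1% |
| 0.20 | 0.255 | 0.228 | 11.8% | 2.8% | 96.0% | 97.6% |

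The power gaps, from unrounded values, are about 0.2, 0.5, 1.0 and 1.6 points.

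**Simulation check** (11 unequal centres, blocks of 4 assumed). Without loss, the planned t-test had size 4.5%, 4.0% and 3.2% at ICC 0.05, 0.10 and 0.20, against about 5% after adjustment.

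**Effect of dropout.** Random loss of 20% disturbs the balance within a centre. For a centre that randomized m patients, the variance of the difference in evaluable counts between arms is m × 0.8 × 0.2 = 0.16m. Under unstratified allocation it would be 0.8m. So 0.16/0.8 = 20% of the between-centre variance returns and the true SE becomes S√(1 − 0.8 × ICC). At ICC 0.05, 0.10 and 0.20 the size is then about 4.5%, 4.1% and 3.2%. Simulated values with 20% loss were 5.2%, 3.8% and 3.6% (adjusted: 5.5%, 4.9% and 5.0%). At ICC 0.05 the shortfall was too small to see against simulation noise. Loss, like incomplete blocks, therefore shrinks the SE overstatement. It does not clearly shrink the power gap, because the unadjusted estimate itself becomes more variable: simulated power at ICC 0.20 with loss was 95.4% planned against 97.6% adjusted.

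**Scope of the figures.** They concern the primary t-test only. For Mann-Whitney, chi-square and Fisher the direction follows from the same argument, with event rates in place of means for binary outcomes, but no size was computed.

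**The case against.** The best case on the other side is that little is lost. On the stated inputs, power is above 90% in every row. The test errs on the safe side, nothing is biased, and at an ICC of 0.02 the effect is negligible. All of that stands, and it limits the weight of the point.

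It can also be said that centre adjustment is commonly left to a full analysis plan, which is not shown. This carries less weight. The article does not leave the method open; it names an unstratified test for each outcome. The detailed rule for pooling small centres is something a full plan could hold, and its absence is not part of this point.

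A reader might infer four stronger things that the document does not support:

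- **That p-values are too large whenever centres differ.** This holds on average, and only if centres differ in mean outcome or event rate. In the simulation at ICC 0.20 under no treatment effect, the unadjusted p-value was the larger one in about 79% of data sets without loss and about 61% with 20% loss.
- **That the gain from stratification is thrown away.** Blocking improves the estimate whichever test follows. At ICC 0.10, planned power rises from 94.1% to 95.1% and adjustment takes it to 96.1%, so about half the gain is kept.
- **That adjustment lifts power from 94% to as much as 97.6%.** The 94% belongs to an ICC of 0. The planned test at ICC 0.20 has 96.0%, so the gain is 1.6 points.
- **That false positives are inflated.** The error runs the other way.

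**Conclusion.** The point holds as a modest mismatch between design and analysis. If centres differ in outcome, the named tests overstate the standard error on average and are conservative. Over an assumed ICC of 0.02 to 0.20, the primary t-test's standard error is about 1% to 11.8% too large, its true size is 4.8% down to 2.8%, and the power forgone is about 0.2 to 1.6 points. The direction is firm; the size is not, since it depends on an ICC the article does not give and on how well within-centre balance survives dropout and incomplete blocks. The validity of the trial is not threatened. The change is worth making because it costs almost nothing and the reported intervals would then match the way patients were randomized.

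**What to change.** Amend the Statistical Analysis Plan section, before unblinding, as follows:

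- **Continuous outcomes:** a linear model with treatment and centre. Add the baseline value where Follow-Up Procedures collects one: NIHSS and the biological markers. PRO-Stroke and SS-QOL are not listed at baseline, so they get centre only.
- **Where a rank test is needed:** the van Elteren test stratified by centre, in place of Mann-Whitney.
- **Binary efficacy outcomes:** Cochran-Mantel-Haenszel stratified by centre, in place of chi-square or Fisher, for example with a stratified risk difference. This keeps the comparison of proportions that the article describes. Logistic regression with centre would instead give a conditional odds ratio, which is a different effect measure.

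The adverse-event comparisons need not change for this point.

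The article plans no covariate-adjusted model, so the linear model is a new primary method and not merely an added term. It needs no change to recruitment, visits or sample size. The cost is 11 − 1 = 10 degrees of freedom out of about 382, plus a decision before unblinding on whether very small centres are pooled.

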**FIGURE 1 F1:**
[figure not shown]
The flowchart of the EXPECT trial.

### Treatment

Eligible patients will be assigned to the intervention and control groups. The intervention group will receive daily single infusions of 500 mg PNS diluted with 250 ml of 0.9% sodium chloride injection for 10 days. The control group will receive a PNS placebo using the aforementioned protocol. The PNS and PNS placebo will be manufactured and supplied by Guangxi Wuzhou Pharmaceutical (Group) Co., Ltd. with identical appearance, color, and flavor. All patients will receive current guideline-recommended standard treatments, including the basic control of risk factors and anti-platelets for AIS (Powers et al., 2019). Figure 1 presents the treatment assignments. Edaravone and butylphthalide administration will be strictly prohibited during the treatment period. Investigational medicine will be discontinued in case of SAE occurrence, study withdrawal request from the patients or their legally authorized representatives, or poor compliance or non-adherence to the prescribed interventions. We will faithfully record the reasons for discontinuing interventions.

### Study Settings and Recruitment Strategies

Inpatients will be recruited from 11 tertiary hospitals throughout eight provinces in China. Additionally, poster advertisements will be placed in these medical centers to allow the patients to voluntarily contact investigators. Potential patients will be screened for eligibility based on the inclusion and exclusion criteria. Eligible patients will be informed regarding the risks and benefits of the study. Subsequently, patients or their legally authorized representatives will sign the informed consent form if they agree to participate in the study. Patient enrollment of the EXPECT trial began in September 2020. Until December 2020, 13 patients had been enrolled and the estimated primary completion will be October 2022. Figure 2 presents a schematic diagram of the patient timeline.

